### Sample size/power calculation

A sample of 40 participants in each group will be required to observe significant differences in lung function between groups (decrease in FEV_1_ > 10–12 ml/year), in a two-tailed test with a mean FEV_1_ value of 95%, significance level of 5%, 80% strength and less than 15% losses to follow-up [24].

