All participants will receive two years of follow-up. They will be invited to schedule an annual follow-up visit (visits 3 and 5, Figure 1), which will be the same as visit 1 for the group to which they were randomly assigned. Additionally, participants in the intervention group will be invited to an annual group session (visits 2 and 4, Figure 1) midway between the follow-up office visits.

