With the goal of minimizing the possible losses to follow-up, a common concern in long-term projects, and increase the motivation of study participants, a multicomponent intervention has been designed. The use of new technologies has proven useful in health care settings, reducing costs and improving treatment adherence [32]. The creation of the DIET Blog as a nutritional tool 2.0 to reinforce the nutritional education program is intended to increase MD adherence during follow-up. In addition to making recipes and educational materials available periodically, the blog will provide an ongoing “reminder” of the benefits of a balanced diet and facilitate a more agile and flexible interaction between participants in the intervention group and the dietician, beyond their consults in the primary care centre.

With respect to group sessions, the third component of the intervention design, these will be more recreational. In addition to reinforcement of the main items that are characteristic of the MD pattern and the opportunity to clear up any questions or misunderstandings, the sessions will encourage participants to exchange experiences, raise awareness and increase motivation. This will affect the change in attitudes that is absolutely necessary to initiate changes toward eating habits that are healthy and balanced, along with other lifestyle habits such as physical exercise, smoking cessation, etc.

Knowledge and skills are essential to properly evaluate MD adherence in terms of specific foods, as well as to increase the validity and reliability of the information collected using the study questionnaires. Therefore, the expertise of an experienced, highly qualified nutritionist is a fundamental requirement for the success of the nutritional intervention and participant follow-up.

The effect on lung function will be evaluated by comparing the results of three consecutive forced spirometry measurements, taken annually during the three-year project period. Although in theory this time period is sufficient to allow observations about the longitudinal effects of the diet on spirometry values, it could be too short to show statistically and clinically significant differences between the two groups. In any case, these results should provide additional evidence of the effect of a Mediterranean-type dietary pattern on lung function in a population of smokers with no previous respiratory disease.

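### The 80% power claim for a 10–12 ml/year FEV1 difference cannot be derived from the stated inputs, and holds only if the SD of the two-year FEV1 change is at most about 29–38 ml

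*Protocol article*

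**What the plan says.** The Sample size/power calculation section of the protocol article states: "A sample of 40 participants in each group will be required to observe significant differences in lung function between groups". The target and the test are given as "decrease in FEV_1_ > 10–12 ml/year), in a two-tailed test with a mean FEV_1_ value of 95" per cent. The remaining inputs are "significance level of 5%, 80% strength and less than 15% losses to follow-up". The section ends with a literature citation. No SD or other measure of spread for FEV1, its change or its rate of decline appears there or elsewhere in the article.

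Three other places bear on the calculation:
- Intervention: "All participants will receive two years of follow-up".
- Statistical analysis: changes from baseline in lung function are to be compared between the two groups. This is the comparison that the power must describe.
- Discussion: the authors say of the study period that "it could be too short to show statistically and clinically significant differences between the two groups".

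**The concern.** Power for a difference between two mean changes depends on the difference, the SD of the change, the number per group and alpha. The section supplies the difference in ml/year and then, where an SD on that scale would be expected, a mean of 95%, presumably per cent of predicted. That figure is on another scale and is a level, not a spread. It can neither enter the formula nor stand in for the SD.

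The power figure governs how a null result is read. If the trial is taken to have 80% power for 10–12 ml/year, a non-significant result counts against a diet effect of that size. If the real power is much lower, the same result says little about such an effect.

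**Working it through.** **Inputs from the article.** 40 per group, 1:1 allocation, two-sided alpha 0.05, power 0.80, losses below 15%, difference in FEV1 decline of 10–12 ml/year, two years of follow-up. If the yearly difference is constant, the two-year difference is 2 × 10 = 20 ml to 2 × 12 = 24 ml.

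**Forward calculation.** n per group = 2 × [SD × (1.96 + 0.84) / difference]². Without an SD this cannot be evaluated, so the printed 40 cannot be reproduced. What can be done is to solve for the SD that makes it right.

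**Numbers analysed.** 40 × 0.85 = 34, and 34 / 0.85 = 40. Both 34 and 40 per arm are carried through.

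**Required standardised difference.** The normal approximation gives 2.80 × √(2/n): 0.626 at n = 40 and 0.679 at n = 34. The two-sample t test (noncentral t) gives 0.634 and 0.690, used below.

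**Largest SD compatible with 80% power** (difference divided by standardised difference):

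| Evaluable per arm | SD of annual change, 10 / 12 ml | SD of two-year change, 20 / 24 ml |
|---|---|---|
| 40 | 15.8 / 18.9 ml | 31.5 / 37.8 ml |
| 34 | 14.5 / 17.4 ml | 29.0 / 34.8 ml |

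**Meaning per reading.** If every participant declined at exactly the same rate, the SD of a change between two readings would be √2 times the error SD of one reading. The ceilings therefore allow 29.0/√2 = 20.5 ml to 37.8/√2 = 26.8 ml, about 21–27 ml per reading. Any true variation in decline between people lowers this.

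**Power under assumed SDs of the two-year change.** These SDs are assumptions; none is in the document.

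| Assumed SD | 34 per arm, 20 / 24 ml | 40 per arm, 20 / 24 ml |
|---|---|---|
| 50 ml | 37% / 50% | 42% / 56% |
| 100 ml | 13% / 16% | 14% / 19% |
| 150 ml | 8% / 10% | 9% / 11% |

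**What 34 evaluable per arm can do.** Detectable difference at 80% power = 0.690 × SD, which is 69 ml over two years at an assumed SD of 100 ml and 103 ml at 150 ml. The 95% CI half-width = t × SD × √(2/34), with t = 1.997 on 66 degrees of freedom: about 48 ml at SD 100 ml and 73 ml at SD 150 ml.

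**Percentage scale.** If the calculation had really been done in per cent of predicted, an assumed SD of 10 to 15 points would give detectable differences of 6.8 to 10.2 points with 34 per arm (normal approximation). The article states no difference on that scale.

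**The case against.** The strongest reply is that this is a condensed article: the SD may stand in the full protocol or in the cited source, neither of which is shown. That is fair, and a missing SD alone would not justify this point. But any SD held elsewhere must still be at or below the ceilings above for the printed figures to be right. The 95% may also be meant only as a description of expected baseline lung function. In that case it is not a unit error inside a formula, but it still leaves the calculation without an input on the ml scale.

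Another reply is that the Discussion already admits the period may be too short. That caveat makes it less likely that the authors themselves would over-read a null result. It does not correct the 80%, which is stated without qualification. Counting the project as three years, a term the Discussion also uses, would raise the ceiling only to about 44–57 ml (30–36 ml divided by 0.690 or 0.634).

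A reader might infer more than the document supports:
- *That the implied SD is shown to be implausible, or that 10–12 ml/year is shown to be undetectable.* The document has no spirometry variability figure. Both statements depend on an SD still to be supplied.
- *That giving the effect as a range breaks the calculation.* If the sample was sized at 10 ml/year, power at 12 ml/year is about 92%, so at least 80% would hold across the range. Power falls short at 10 ml/year only if 12 was the design value, which the text does not say.
- *That the loss allowance is inconsistent.* 34 / 0.85 = 40 exactly, so 40 enrolled with 15% losses allowed for is a coherent reading.

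**Conclusion.** The point stands in conditional form. The printed inputs do not yield 80% power. The document's own figures make the claim true only if the SD of the two-year FEV1 change is at most about 29–35 ml with 34 evaluable per arm, or 32–38 ml with 40. This ceiling assumes a constant yearly difference, a two-sample comparison of change from baseline and the two-year follow-up; it needs no outside data. How far power falls short, if it does, depends on the true SD: at an assumed 50 ml it is already 37–56%, and at 100 ml 13–19%. The documents do not establish which applies, so the trial should be called unsupported at 80% power for this effect, not proven underpowered. It is worth correcting before results are read, because the stated power determines what a null finding means.

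**What to change.** Keep 40 per group and replace the 80% statement with a calculation on one scale: change in FEV1 in ml from visit 1 to visit 5, with 34 evaluable per arm. Take the SD of that change from spirometry already held on RESET participants. The Discussion makes such data a condition for entry, although an SD of change needs repeat readings on the same person. If there are none, state a range of SDs and its basis.

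Report the detectable difference (0.69 SD, for example 69 ml over two years at an assumed SD of 100 ml) and the expected 95% CI half-width (about 48 ml at the same SD). If the SD exceeds about 29 ml for a 10 ml/year difference, or 35 ml for 12 ml/year, say that the trial does not have 80% power for that effect and that a null result will be interpreted from the confidence interval.

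The cost is wording and one small calculation, with no extra participants or visits. The downside is that the stated power will probably look less favourable. Using FEV1 for this statement does not settle how the three spirometric measures named as primary are to be handled, which is a separate matter.

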### Statistical analysis

The study will use an intention-to-treat analysis and the main outcome variable will be measured at the beginning of the study for each participant. The effectiveness of the simple randomization will be evaluated by the comparability and homogeneity of the two groups in terms of the baseline distribution of the study variables. Losses to follow-up will be calculated for each group and evaluated to determine whether the proportion of losses is independent of assignment to the intervention or control group.

Qualitative variables will be described as frequencies or percentages and quantitative variables by means and standard deviations if they follow a normal distribution, or median and interquartile range.

Variables will be stratified by study group; basal comparison will be done by x^2^ test for qualitative variables and Student t or Mann–Whitney U for quantitative variables. Data from the initial MD Adherence Questionnaire and Food Frequency Questionnaire (V1) will be compared to the final questionnaire data (V5). In addition, changes from baseline in lung function after the corresponding nutritional intervention, will be compared for both groups. If important clinical differences are observed, multivariate analysis will be used to determine which factors are independently associated with the outcomes, adjusting for covariates such as age, sex, ethnic group, height, BMI, education level, smoking habit, physical activity or total caloric intake [6]. The results will be presented using relative measures including relative risk (RR) and relative risk reduction (RRR), and absolute risk reduction (ARR), with 95% confidence intervals. All analysis will be done with SPSS version 22.0, considering differences to be significant when *p* < 0.05.

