**Methods/design:**

Randomized, controlled, parallel clinical trial. Setting: primary health care centers in Catalonia (Spain). Participants: Current smokers (cumulative > 10 pack-years) aged 35–70 years, with Internet access, who provide signed informed consent to participate. Intervention: A nutritionist will conduct a 2-year multicomponent intervention to increase MD adherence, based on: 1) a personalized dietary-nutritional education intervention, 2) a Web 2.0 approach, the DIET Blog of nutritional information, and 3) group sessions to increase motivation to increase MD adherence and motivation to make changes in eating habits. Annually, an office visit and one group session will reinforce the nutritional intervention. The control group will follow their usual diet, with general nutritional counselling. In both groups, a 14-item questionnaire will evaluate individual MD dietary patterns and forced spirometry will assess lung function. Analysis: Intention to treat. The unit of analysis will be the individual smoker. Primary outcome is lung function indicated by spirometry, FVC, FEV1 and FEV1/FVC %. Lung function parameters in both groups will be compared by adherence to the MD pattern.

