### Control group

In a visit lasting about 30 minutes (visit 1), control group participants will provide the necessary study data and receive written dietary recommendations appropriate to their clinical-metabolic situation (advice to control weight, glycaemia, cholesterol, blood pressure, etc.). These patients will then be directed to their family nurse and/or doctor to complete the study’s medical testing: spirometry, 12-lead electrocardiogram and blood tests.

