### Measures

All participants will be contacted by telephone to schedule the **inclusion visit (visit 1)**, which will include the standardized medical tests and completion of a data collection questionnaire containing the following information:Sociodemographic and family data: age, sex, ethnicity, marital status, number of children, education level, socioeconomic status, employmentHistory of diseases and respiratory symptomsTobacco use: current number of cigarettes/day), cumulative consumption (packs/year) and age when the participant started smokingDietary habits and lifestyleAlcohol use, measured in units/week (one unit = 10 gr alcohol)Food Frequency Questionnaire [20]Questionnaire on MD Adherence (14 points) [21]Minnesota Leisure Time Physical Activity Questionnaire, validated for the population of Spain [22]Basic physical examination, including weight (Kg), height (cm), body mass index (BMI = Kg/m^2^), waist circumference (cm) and blood pressure (mmHg)Exhaled carbon monoxide measured by carboximetry12-lead electrocardiogramBasic blood tests to measure glucose, triglycerides, cholesterol (total, high-density lipoprotein and low-density lipoprotein, creatinine and transaminases (aspartate-aminotransferase and alanine-aminotransferase).Forced spirometry and bronchodilation test to obtain FVC and FEV_1_ values and the FEV_1_/FVC% ratio, following current guidelines [23].

The primary outcome variable to determine whether the objective has been met will be the change in lung function indicated by spirometry, FVC, FEV_1_ and FEV_1_/FVC %. The secondary outcomes variables will be changes in MD pattern, anthropometric measurements (weight, BMI and waist circumference) and smoking habit.

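### The stated analysis of change in Mediterranean Diet adherence is V1 versus V5 with no between-arm comparison of change, so it cannot show that the intervention raised adherence more than control

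*Protocol article*

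**What the plan says.** The Statistical analysis section of the protocol article treats the two outcomes in neighbouring sentences. For diet: "Data from the initial MD Adherence Questionnaire and Food Frequency Questionnaire (V1) will be compared to the final questionnaire data (V5"). For lung function, introduced as an addition: "changes from baseline in lung function after the corresponding nutritional intervention, will be compared for both groups". Just before these comes a general statement: "Variables will be stratified by study group; basal comparison will be done by x^2^ test for qualitative variables", with Student t or Mann–Whitney for quantitative variables.

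The Measures section lists the secondary outcomes as "changes in MD pattern, anthropometric measurements (weight, BMI and waist circumference) and smoking habit". The Background gives the intervention a comparative purpose: to raise adherence relative to the participant's usual diet.

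Both arms supply the data. The abstract says: "In both groups, a 14-item questionnaire will evaluate individual MD dietary patterns and forced spirometry will assess lung function". Under Intervention, the annual visits 3 and 5 are described as visits "which will be the same as visit 1 for the group to which they were randomly assigned". Under Control group, controls "receive written dietary recommendations appropriate to their clinical-metabolic situation".

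**The concern.** The diet sentence contrasts two time points. The lung-function sentence contrasts two randomised groups. Only the second kind of contrast uses the randomisation to attribute a change to the intervention.

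A before-after rise could have other causes here. Controls are given dietary recommendations and answer the same questionnaires each year, and the Discussion acknowledges that this information is subjective. Scores in both arms can therefore move without any effect of the MD programme.

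What is at stake is the interpretation of the trial. The Discussion concedes that follow-up may be too short to show a difference in lung function. If the lung result is null, readers will ask whether diet diverged between the arms. A significant V1 to V5 rise in the intervention arm, or significance in that arm and not in the other, could be taken as proof that it did.

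**Working it through.** **Plan's own figure.** The article states no sample size, effect or SD for adherence. Its 40 per group is for FEV1 and is used here only to set the number of completers: 40 × (1 − 0.15) = 34 per arm, taking losses at the stated 15% limit.

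**Assumed inputs.** Both arms rise by the same amount, so the true between-arm effect is zero. The shared rise, in units of the SD of change (c), runs from 0.2 to 0.67. On the 14-point score, the upper part corresponds to rises of 0.75–1.0 points with an SD of change of 1.5–2.0:

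- 0.75/2.0 = 0.375
- 0.75/1.5 = 0.5 and 1.0/2.0 = 0.5
- 1.0/1.5 = 0.67

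None of these values comes from the article.

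**Before-after test in one arm.** Paired t test, n = 34, 33 df, two-sided 5%, critical value 2.035. The noncentrality is c√34 = 5.831c, and p is the probability of a significant result.

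**Intervention arm alone significant.** With independent arms and the same p in each, the probability that the intervention arm is significant and the control arm is not is p(1 − p). Its maximum is 0.25, at p = 0.5.

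| Shared rise c | 5.831c | p, intervention arm | p(1 − p) |
|---|---|---|---|
| 0.2 | 1.17 | 0.20 | 0.16 |
| 0.3 | 1.75 | 0.40 | 0.24 |
| 0.375 | 2.19 | 0.56 | 0.25 |
| 0.5 | 2.92 | 0.81 | 0.16 |
| 0.67 | 3.89 | 0.965 | 0.03 |

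If the arms were pooled (n = 68), the same test would be significant in about 37% of trials at c = 0.2 and 68% at c = 0.3.

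**Between-arm test.** The estimate is (mean change, intervention) − (mean change, control). An equal rise cancels, so the test rejects in 5% of trials whatever c is.

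**Would the between-arm test be informative at this size?** By the normal approximation, power for a true difference of d SDs of change is Φ(d√(34/2) − 1.96) = Φ(4.123d − 1.96):

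- d = 0.5: Φ(0.10) = 0.54
- d = 0.69: Φ(0.88) = 0.81
- d = 0.8: Φ(1.34) = 0.91

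These values of d are also assumptions.

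**The case against.** The other side has a good deal to say.

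- **The control arm is not ignored.** A reader might infer from the V1 versus V5 sentence that controls drop out of the diet analysis. The documents do not support that. The questionnaire is given in both groups, visits 3 and 5 repeat visit 1 in each arm, and variables are to be stratified by study group. The sentence may well mean V1 versus V5 by arm.
- **It is not the only use of adherence.** The abstract also plans to compare lung function by adherence, and adherence falls under the general baseline comparison. Neither use tests whether the intervention raised adherence.
- **A between-arm comparison is not excluded.** The sentence names no test and could be read as merely defining the change. The section later promises relative and absolute risk measures with confidence intervals, which normally compare groups, and adherence has low, moderate and high categories. This stands as far as it goes, but the article does not link those measures to adherence. The contrast it does attach to the diet questionnaires is the one between visits.
- **Detail may sit in a fuller document.** That would answer a point about a missing model. Here the article names a contrast for this outcome, and a different one for lung function in the next sentence.
- **The large percentages can mislead.** A reader might take 20–97% as a false-positive rate. It is the power of a paired test to detect a rise that really occurred; harm arises only if that rise is credited to the intervention. An equal rise is itself conjecture: the control advice concerns weight, glycaemia, cholesterol and blood pressure, and is not described as MD education.
- **The primary outcome is untouched.** Lung function has its own between-group comparison of change, which does not depend on the adherence analysis.

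**Conclusion.** The point holds in a limited form. As written, the analysis of change in MD adherence compares V1 with V5 and specifies no between-arm comparison of change. Stratifying by arm does not repair this, because setting significance in one arm against non-significance in the other is not a test of the difference.

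Under an assumed equal rise of 0.2–0.67 SD with 34 completers per arm, the intervention arm shows a significant rise in about 20–97% of trials. The intervention arm alone does so in about 3–25%. The second range measures the one-arm-only misreading directly. Both depend wholly on the assumed rise, and on independent arms with equal SD of change. A between-arm test holds 5% without any assumption about the size of the shared rise.

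The text should be corrected because it affects a key secondary outcome and how the lung-function result will be explained. It does not affect the validity of the primary comparison.

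**What to change.** Replace the diet sentence in Statistical analysis with wording such as: *The 14-point MD adherence score at V5 will be compared between the randomised groups, adjusted for the V1 score, and the mean difference reported with its 95% confidence interval. Change from V1 to V5 within each group will be reported descriptively.*

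A between-arm comparison of change scores would also answer the question; adjusting for V1 is the form recommended here. Using the V3 score as well, and testing food frequency intakes between groups, are optional. If intakes are tested, the chosen ones should be named in advance.

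The cost is one sentence. The questionnaires are already administered yearly in both arms, so no visit, participant or measurement is added.

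### The lung-function test is an unadjusted change score and losses are checked only by proportion, which is weak support for the stated intention-to-treat analysis; a repeated-measures model should be prespecified

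*Protocol article*

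**What the plan says.** The Statistical analysis section states intention to treat. For the primary outcome it says that "changes from baseline in lung function after the corresponding nutritional intervention, will be compared for both groups". It names no covariate for that comparison. A multivariate analysis, with covariates such as age, sex, height, BMI and smoking, is made conditional on seeing clinically important differences.

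On attrition, the section has losses counted per group and "evaluated to determine whether the proportion of losses is independent of assignment to the intervention or control group".

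The Discussion says that the effect on lung function will be judged by comparing "three consecutive forced spirometry measurements, taken annually". The Intervention section places annual office visits for both arms at visits 3 and 5, after the inclusion visit (visit 1). In the analysis section, visit 5 is named only for the two diet questionnaires; the lung-function sentence names no visit.

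The Sample size section sets 40 per group for a "decrease in FEV_1_ > 10–12 ml/year", with "significance level of 5%, 80% strength and less than 15% losses to follow-up". It gives "a mean FEV_1_ value of 95" per cent but no standard deviation.

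**The concern.** A randomised participant with no spirometry after baseline has no change score. A participant lost after year 1 has a one-year change but no two-year change, and the text does not say which of these counts. The only stated step on attrition compares how many are lost in each arm. Bias depends on who is lost, not only on how many.

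Different patterns of loss by arm are plausible here. The Discussion says the multicomponent programme was designed partly to limit losses, and only the intervention arm receives the blog and group sessions. Controls have a shorter visit and are sent to their own nurse or doctor for spirometry. Loss rates could match while the kind of participant lost differs.

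Making adjustment depend on what is observed also leaves the primary estimate open until the data are seen. At stake is a between-group difference of only 20–24 ml over two years, which a modest selection effect can shift noticeably.

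**Working it through.** **Inputs from the protocol article.** 40 per group, 1:1; two-sided 5%; 80% power; losses below 15%; target 10–12 ml/year, so 2 × 10 to 2 × 12 = 20–24 ml over two years.

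**Input not given: the SD of FEV1 change.** The stated 40 per group therefore cannot be reproduced. Back-solving, SD = δ / [(1.960 + 0.842) × √(2/n)]:
- n = 40: 10 / (2.802 × 0.2236) = 16.0 ml/year; for δ = 12, 19.2. Over two years: 32–38 ml.
- n = 34 (40 less 15%): 14.7–17.7 ml/year, or 29–35 ml over two years.

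Two assumed values bracket the question: about 30 ml (close to what 40 per group implies) and 104 ml. The second comes from an assumed slope SD of 30 ml/year and reading-error SD of 60 ml: √(4 × 900 + 2 × 3600) = 104.

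**Why equal proportions are not enough.** With the same fraction d lost in both arms, the bias of a completer comparison is d × (gap_I − gap_C), where gap is the mean change in retained minus lost participants. It is zero only if the gaps match. At d = 15%, a bias of half the target (5–6 ml/year) needs a gap difference of 5/0.15 to 6/0.15 = 33–40 ml/year; at 10%, 50–60; at 5%, 100–120.

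**Power of the loss check, 10% v 20%, 40 per arm.** Pooled p = 0.15. SE under the null = √(2 × 0.15 × 0.85/40) = 0.0798; SE under the alternative = √((0.09 + 0.16)/40) = 0.0791. Power = Φ[(0.10 − 1.96 × 0.0798)/0.0791] = Φ(−0.71) = 24%. By the same formula, 5% v 15% gives 32% and 15% v 30% gives 36%.

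**Size of the bias.** Assumptions: no true effect, equal loss in both arms, random loss in controls, and loss in the intervention arm after visit 3 that is more likely the worse the year-1 change.

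At SD 104 ml, the SD of year-1 change is √(900 + 2 × 3600) = 90 and its covariance with two-year change is 2 × 900 + 3600 = 5400, so the regression slope is 5400/8100 = 0.667. The ceiling, reached if exactly the worst fraction d leaves, is [φ(z_d)/(1 − d)] × 90 × 0.667. The simulated column lets the log-odds of leaving rise by 0.5 to 2 per SD of worse year-1 change.

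| Loss per arm | Ceiling (ml) | Simulated bias (ml) |
|---|---|---|
| 5% | 0.109 × 60 = 6.5 | 1.5–4.7 |
| 10% | 0.195 × 60 = 11.7 | 2.9–8.6 |
| 15% | 0.274 × 60 = 16.5 | 4.4–12.1 |

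Weaker dependence brings the lower end to about 1 ml, so the range is about 1–12 ml.

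At SD near 30 ml the range is about 0.5–6 ml. The 15% ceiling depends on how the SD splits between true slope and reading error: 16.5 × 30/104 = 4.8 ml with the same split, and 0.274 × 30 = 8.2 ml with no reading error. The upper end therefore needs strong selection and mostly real variation in decline.

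**Same data, year-1 value used.** Regressing two-year change on year-1 change in those retained, and averaging the predictions over everyone, gives bias within 0.1 ml of zero. This follows from the assumption that loss depends only on observed values.

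**Precision in complete cases.** Baseline adjustment multiplies the change-score variance by (1 + ρ)/2. For an assumed ρ of 0.90–0.98 that is 0.95–0.99, a saving of 1–5%.

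**The case against.** The strongest reply is that much of this is an unstated missing-data method, which a journal article commonly leaves to the full protocol or analysis plan. That stands, and the absence of such a method is not the point made here. The point concerns what the article does state: an unadjusted change score, adjustment triggered by the data, and a comparison of loss proportions.

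Four stronger readings are tempting, and the document does not support them.
- **Only completers are analysed.** No completer set is stated, and the lung-function sentence names no final visit. Someone lost after year 1 still has a change from baseline.
- **The year-1 spirometry has no role.** The Discussion gives all three readings a role. What is unclear is how the year-1 reading enters the test.
- **The exclusion criterion about people who have declined to go on with the study removes dropouts after randomisation.** The Intervention section applies the eligibility criteria before consent and allocation, and candidates come from the earlier RESET trial. At most this wording needs clarifying.
- **The bias exceeds half the target effect.** At 12 ml it would be 12/24 to 12/20, or 50–60%, but that needs an assumed SD about three times what 40 per group implies, the full 15% loss and strong selection in one arm. Much of the selection in that scenario is on spirometer noise: 3600 of the 5400 covariance is shared baseline reading error.

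It is also fair that the article never calls the loss check a safeguard, and that reporting loss by arm is good practice. The limit on what the check can show remains.

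**Conclusion.** The concern holds in a limited form. The stated comparison and loss check do not secure the intention-to-treat claim: equal proportions are compatible with bias, and the check would miss most real differences in loss at this sample size. Reliance on completers would cost about 1–12 ml at an assumed two-year SD of 104 ml (up to 50–60% of the target) and about 0.5–6 ml at an SD near 30 ml (up to 25–30%). These figures rest on an SD the document does not give, on 5–15% loss, and on outcome-related loss in one arm; they describe a possible range, not an expected bias. If the same patterns of loss occur in both arms, the bias is zero. If informative loss runs in opposite directions in the two arms, it is larger. The near-zero bias of the alternative analysis holds only when loss depends on observed values. The change is worth making because it is cheap and settles the primary analysis before the data are seen.

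**What to change.** Prespecify as primary a mixed model for repeated measures using FEV1 at visits 1, 3 and 5, with group, visit, group-by-visit interaction, baseline FEV1, sex and height, including every randomised participant with any spirometry. Baseline should enter in one way only: as the first response with a common mean in both groups, which keeps people with baseline alone in the model, or as a covariate for visits 3 and 5. The estimate is the group difference at visit 5. Drop the rule that adjustment depends on observed differences.

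Add one sensitivity analysis for data missing not at random, for example shifting the unobserved values in one arm by a range of amounts. Keep loss by arm as description. State in the analysis section how the year-1 reading is used, so that it agrees with the Discussion, and clarify that the criterion on declining to go on refers to refusal before randomisation.

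The cost is slightly more analysis work in SPSS, which is already specified, and no new data. The precision gain for complete cases is small; the benefit is for participants lost after visit 3 and in having a fixed primary analysis.
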